### Trial status

We started recruiting patients to the trial in September 2014. Recruitment will run for 1 year, with data collection complete by end-December 2015.

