**Results:**

Recruitment started on 26 September 2014 and will run for 1 year.

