### Recruitment

Clients will attend their assessment appointment with an alcohol counsellor as usual. If the alcohol counsellor considers the client meets the inclusion criteria for the trial (detailed above) they will discuss the trial with the client and provide written information and ask them to sign the consent form if they express interest in taking part. The client will be given a 24-hour “cooling off” period to decide whether or not to proceed.

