### Data collection

If the client wishes to participate, they will be allocated a trial identification number linked to their email address and mobile phone number. All data will be collected anonymously online. All participants will be emailed a link to complete the baseline data collection questionnaires (see outcome measures, below). After they have completed the questionnaires, they will then be individually randomised by computer to the intervention or TAU. Those randomised to the intervention will be emailed a link to HeLP-Alcohol and those randomised to TAU will be directed back to their community alcohol service. All participants will be emailed another request for follow-up data collection 3 months after randomisation. For those participants who do not respond to the first email, there will be another two follow-up emails and then a phone call or text message request. See Fig. 1 for CONSORT participant flow diagram [21].

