### Outcome measures

#### Primary outcomes

Recruitment as a percentage of eligible patients.Retention measured by completeness of online data collection for each arm at baseline and at 3 months as a percentage of patients randomised.

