### Statistical analysis

As this is a feasibility RCT, no hypothesis is to be tested. The aim of the trial is to determine estimates of recruitment and retention rates, to determine acceptability of the intervention and to provide parameters for the power calculation for a Phase 3 trial. Success criteria for recruitment and retention will be 84 and 75 %, respectively, as per the UKATT trial [30].

The analysis will be mainly descriptive. Descriptive statistics will be used to compare demographic characteristics of those completing each arm of the trial with those lost to follow-up. We will use multivariate logistic regression with robust confidence intervals (CI) to examine the impact of age, gender, ethnicity and deprivation level on these outcomes.

We will perform an analysis using regression of outcome on randomised group, adjusted for baseline value of outcome (for those outcomes measured at baseline) and other variables (age, gender, ethnicity and deprivation level) to compare the two arms using the following outcome measures at 3 months. Differences between the intervention and control groups for continuous variables with skewed distribution, e.g. alcohol consumption, will be log transformed, following a similar analysis to that by Wallace et al. [31]:Change in mean unit consumption of alcohol per week;Change in AUDIT score;Change in level of current psychological global distress score;Change in self-efficacy score;Acceptability of intervention using CSQ-8;Use of additional sources of support accessed during the trial period.

For the intervention group, we will examine adherence to the intervention, measured through automated recording of numbers of log-ins and numbers of pages visited at each log-in. We will conduct within-group analysis using linear regression to examine the impact of age, gender, ethnicity and deprivation on use of the intervention (number of log-ins, number of pages accessed, number of modules completed).

Missing data will be handled as follows:The primary analysis will be the mean difference in changes from baseline in all outcome variables between intervention and control groups at 3 months, using all available results but without imputation of missing data. Secondary analyses will include all randomised individuals by assuming that non-responders have no change in any missing outcome measures;For use of the intervention, data will be largely complete as automatically collected by the website.

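### The stated close of data collection leaves about 5 days at most after the last nominal 3-month request, so late recruits may miss reminders and retention may be slightly understated

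*Protocol article*

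**What the plan says.** Four parts of the protocol article set the timetable.

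- **Recruitment period.** Abstract, Results: "Recruitment started on 26 September 2014 and will run for 1 year".
- **Close.** Trial status: "Recruitment will run for 1 year, with data collection complete by end-December 2015".
- **Follow-up.** Data collection: "All participants will be emailed another request for follow-up data collection 3 months after randomisation". For non-responders, "there will be another two follow-up emails and then a phone call or text message request". No interval between contacts is given.
- **From recruitment to randomisation.** The Recruitment section allows a 24-hour cooling-off period. The online baseline follows, and Data collection states: "After they have completed the questionnaires, they will then be individually randomised by computer to the intervention or TAU".

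Two further parts say how retention is used. Primary outcomes: "Retention measured by completeness of online data collection for each arm at baseline and at 3 months as a percentage of patients randomised". Statistical analysis: "Success criteria for recruitment and retention will be 84 and 75" per cent respectively. The Sample size section sets a target of 200 participants.

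**The concern.** One year plus 3 months takes the timetable almost exactly to the stated close. No allowance is visible for the three further contacts that non-responders are promised, or for the interval between joining the study and being randomised. The few days that remain are the last of December.

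Retention at 3 months is one of two primary outcomes, and testing the online follow-up procedure is one of the trial's aims. A late recruit who has not answered when collection stops stays in the denominator and counts as not retained, even if later reminders would have produced an answer. The error can run in only one direction. It would mix a calendar effect into a figure that is compared with a fixed criterion and used in planning Phase 3.

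**Working it through.** **1. The stated date.** 26 September 2014 + 1 year = 25 or 26 September 2015. Adding 3 months gives 25 or 26 December 2015, which is compatible with completion by the end of December. The first request to the last recruit fits; the question is what room is left after it.

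**2. Days left to 31 December 2015.**

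| Delay from last recruitment day (25 or 26 Sept) to randomisation | 3-month date | Days left |
|---|---|---|
| 0 days | 25 or 26 Dec | 6 or 5 |
| 1 day (cooling-off only) | 26 or 27 Dec | 5 or 4 |
| 3 days (assumed) | 28 or 29 Dec | 3 or 2 |
| 7 days (assumed) | 2 or 3 Jan 2016 | none |

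Randomisation on 30 September gives 30 December. Randomisation on 1 October gives 1 January 2016, after the close. About 5 days is therefore the upper end of the margin.

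**3. How many participants could be cut short.** Inputs from the article: 200 participants over 1 year. Assumptions: even accrual, a margin of 5 days, strict closure on 31 December, and a sequence of w weeks.

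Affected = (w − 5/7) × 200/52.

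**4. Effect on retention.** Assume that true retention is 75% and that truncated participants respond at 50%.

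Drop = (0.75 − 0.50) × affected/200.

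| Sequence | Affected | Drop (points) | Chance of at least 150 of 200 |
|---|---|---|---|
| no truncation | 0 | 0 | 54% |
| 1 week | 1.1 | 0.14 | 52% |
| 2 weeks | 4.9 | 0.6 | 46% |
| 4 weeks | 12.6 | 1.6 | 34% |
| 6 weeks | 20.3 | 2.5 | 24% |

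The last column is the binomial probability of reaching the 75% criterion at the reduced rate, both arms pooled. A sequence of 5 days or less gives no drop.

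**5. Dependence on true retention.** The same model, with drop = (true rate − 0.50) × affected/200:

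| True retention | No truncation | 2 weeks | 4 weeks | 6 weeks |
|---|---|---|---|---|
| 70% | 7% | 5% | 3% | 2% |
| 78% | 87% | 81% | 69% | 56% |
| 80% | 97% | 94% | 87% | 77% |

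**6. Dependence on the delay before randomisation.** With a 7-day delay (assumed), a day-by-day count gives about 4, 8, 16 and 24 participants affected for sequences of 1, 2, 4 and 6 weeks. At the same 25-point loss of response the drops are 25 × 4.4/200 = 0.6, 25 × 8.2/200 = 1.0, 25 × 15.9/200 = 2.0 and 25 × 24.1/200 = 3.0 points.

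**7. Scale.** The standard error of a 75% rate is √(0.75 × 0.25/200) = 3.1 points for the whole trial and √(0.75 × 0.25/100) = 4.3 points for one arm of 100.

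**The case against.** A reader might infer from the dates that late recruits cannot receive the reminders and that retention is biased low. The article does not support either statement.

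- Reminder spacing is not given, and a sequence of 5 days or less with prompt randomisation would fit. A condensed article may leave spacing and closing rules to the full protocol, so their absence is not itself a fault.
- The end-December date is a rounded forecast of trial status. No database lock is described, and no rule says that an answer arriving in January is refused.
- Even accrual up to 200 is an assumption. The Discussion warns that eligible clients may not present in sufficient numbers.
- The 50% response in truncated participants has no source in the article.

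A reader might also infer that the truncation would reverse the feasibility decision. The Statistical analysis section says that no hypothesis is tested and that the analysis is mainly descriptive, and no automatic consequence is attached to missing 75%. The changes in the chance of passing are largest close to the threshold. At 70% the criterion would probably be missed in any case, and at 80% it would probably still be met. Nor does a shift of a point or two seriously disturb the Phase 3 assumption of 75% follow-up, which refers to 12 months and comes from an earlier trial.

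These objections limit the size and certainty of the point. They do not remove it: the published dates leave a four-contact sequence at most about 5 days, and none for someone randomised in October. Being smaller than one standard error is only a partial defence, because this error always runs downward and adds to sampling error.

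**Conclusion.** The point holds in conditional form. On the published dates, the last participants may not receive the full reminder sequence, so the primary retention percentage may be understated. The understatement is about 0.1 to 2.5 points for sequences of 1 to 6 weeks, given true retention of 75%, even accrual of 200, randomisation by about 26 September 2015, strict closure on 31 December and 50% response in those cut short. It is nil for a sequence of 5 days or less and reaches about 3.0 points with a 7-day delay and a 6-week sequence. All of these values are below one standard error of the overall rate, 3.1 points. The effect matters only if observed retention lies near 75%. The dates are still worth reconciling, because the error is one-sided, falls on a primary outcome and costs little to avoid.

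**What to change.** Define the close of data collection as last randomisation plus 3 months plus the full reminder window, a few weeks into 2016. With no delay before randomisation, windows of 14, 21 or 28 days (assumed) after 26 December 2015 end on about 9, 16 or 23 January 2016. Alternatively, set a last randomisation date early enough for the sequence to finish by the end of December 2015.

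Keep retention among all randomised patients as the primary measure, as Primary outcomes defines it. If some participants are still cut short, also report retention among those given the complete sequence, as a supplement and not a replacement, because restricting the denominator would change the stated outcome.

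The cost is a database that closes a few weeks later, or recruitment that stops slightly earlier with correspondingly fewer participants.

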## Discussion

Hazardous and harmful alcohol use is a growing problem in the UK. Face-to-face treatment is only accessed by around 10 % of those who could benefit, for several reasons, of which the most important are lack of provision, stigma and inconvenience. We have developed a psychologically informed web-based alcohol programme which may help fill this gap in access, but its effectiveness, cost-effectiveness and equality of access compared with usual treatment in community alcohol services need to be ascertained in a fully powered RCT. The results of this feasibility RCT will provide useful evidence for commissioners of alcohol services as previous studies of web-based treatments for hazardous and harmful alcohol use have been conducted mainly online, for example, comparing websites with and without interaction or feedback [31].

Conducting a Phase 3 RCT to compare a web-based alcohol treatment programme with face-to-face community alcohol treatment is likely to face challenges, hence the need for the feasibility study. Recruitment and retention rates in the feasibility RCT will give an indication of the acceptability of the trial to patients with problem alcohol use. Other methods such as qualitative interviews may give a better idea of acceptability or otherwise, both of the trial and the intervention, and we aim to undertake a separate qualitative study with participants and alcohol counsellors in due course. However, it may not be possible to get the views of people who decline to participate in the trial as they are likely to decline to take part in a qualitative study as well. It is also not possible to determine the characteristics of those who decline to take part as we are not able to collect their demographic data if they have not consented to be in the study. However, we will have access to summary data for all clients seen by a service as the services collect this data for their own evaluations, so this may give us some indication of the characteristics of those who decline to participate compared with those who consent.

It may be that potentially eligible clients do not wish to participate in a trial where there is a chance of being randomised to a website when they may have a preference for face-to-face counselling, or they may not have easy access to a computer, or feel confident using a computer. If they mention a reason for not participating when their alcohol counsellor discusses the trial with them, then we may pick this up from the qualitative interviews with counsellors.

Alcohol counsellors themselves may not find it acceptable to recruit people to a trial where they have a 50 % chance of being randomised to a website. The counsellors may only ask people who they think will be computer-literate, or may not ask those who they worry might disengage with the service if they are not seen face-to-face (selection bias). There may be other reasons why counsellors do not recruit potential recruits which may come out in the interviews, including time pressures and competing priorities.

We chose community alcohol services to as a recruitment setting because we expected that our target population would present to these services in sufficient numbers. However, as we are excluding hazardous or harmful drinkers who have co-morbidities or complex problems such as other substance misuse, eligible clients may not in fact present in sufficient numbers to recruit successfully from this setting.

As previously discussed, attrition from online programmes and online trials is a common problem [17]. We hope to overcome this using text message, email and telephone prompts as previous studies suggests such prompts can improve engagement [32]. We will also collect data on other sources of help accessed during the study, participants’ satisfaction with the intervention and estimates of health professional time for each arm, which will inform the main trial.

The proposed feasibility study is therefore important in order to identify these challenges prior to designing the Phase 3 trial, to test online data collection, randomisation methods and the prompts to encourage continued use of the intervention. Data from this study will also be used to refine the sample size calculation for the Phase 3 RCT. Our hypothesis is that supported access to HeLP-Alcohol is of equal effectiveness as TAU. The RCT will be designed to have 90 % power to detect (at a 5 % significance level) a difference in mean weekly alcohol consumption of 15 % between intervention and TAU groups (if such a difference occurs). The assumptions are (i) standard deviation of alcohol consumption at follow-up is equal to 85 % of the mean and (ii) a correlation between baseline and follow-up alcohol consumption of 0.40, as found in a previous RCT of an online alcohol intervention [30]; (iii) a follow-up rate of 75 % at 12 months, based on the experience of UKATT [33]; (iv) an intra-cluster correlation of 0.02 for the effect of alcohol counsellors, also based on the UKATT trial. The standard error of the mean difference in alcohol consumption will be about 5 %, so an estimated zero difference would have a 95 % confidence interval of −10 to +10 %. The definitive trial therefore requires 1665 participants.

If the definitive study shows that a web-based alcohol treatment programme is as effective as face to face treatment, then implementation of such a programme could increase patient choice, improve access to alcohol treatment for hazardous and harmful drinkers and lead to cost savings for treatment services and more widely for the NHS in treating alcohol-related health conditions, particularly for people who are reluctant or unable to attend face-to-face services.

## Abbreviations

A&E: accident and emergency
AUDIT: Alcohol Use Disorders Identification Test
AUDIT-C: Alcohol Use Disorders Identification Test, Consumption
CSQ-8: Client Satisfaction Questionnaire
CORE-10: Clinical Outcomes in Routine Evaluation (10 item)
EQ-5D: Euroqol 5-dimensions
FAST: Fast Alcohol Screening Test
HeLP-Alcohol: Healthy Living for People who use Alcohol
IBA: identification and brief advice
NHS: National Health Service
NRES: National Research Ethics Committee
SCQ-8: Situational Confidence Questionnaire (8 item)
SBI: screening and brief intervention
TAU: treatment as usual
TOT-AL: TOTal past week ALcohol consumption
UK: United Kingdom
WHO: World Health Organization
